### Analysis of secondary outcome measures

Secondary outcomes will be analysed in a similar manner using appropriate generalised linear models. Linear mixed models will be used to analyse Qualiveen and PDQ-8, along with the primary outcomes measures taken at 6 weeks. Bladder diary data will be used to analyse frequency (using oisson regression) and nocturia (using binary logistic regression).

### Interim analyses

No interim analyses are planned.

### Additional analyses

#### Subgroup analysis

Subgroup analyses will be carried out on reported symptom severity and treatment category. Stricter levels of statistical significance (p<0.01) will be sought, reflecting the exploratory nature of these analyses.

#### Economic analysis

The economic analysis will be a within trial evaluation to estimate the cost-effectiveness of TTNS compared with sham TTNS. This evaluation will be conducted from a UK NHS perspective.

The resources required to provide the TTNS treatment will be recorded by the researchers: this will include equipment costs; staff time; training required; and consumables. Participants will complete simple resource use questionnaires at 6 weeks and 12 weeks to record relevant healthcare resource use. Costs will be attached to resource use using appropriate local or national unit cost data, including the Personal and Social Sciences Research Unit^41^ and NHS Reference Costs.^42^ This will demonstrate likely costs of providing TTNS and show key drivers of costs for PwP. Medication will also be recorded at these time points and costs attached using the British National Formulary.^43^

The resource use data will be combined with the coprimary outcome measures in a cost-effectiveness analysis. The results will be presented as a mean incremental cost per unit change in the ICIQ-UI SF and the mean incremental cost per unit change in the IPSS.

### Methods to handle protocol non-adherence and missing data

The analysis will be intention to treat with no account taken of protocol non-adherence. Non-compliance to randomised allocation is not anticipated as participants are blinded throughout.

The extent of missing data will be explored in the outcomes, especially the primary outcomes. Patterns of missing data will be explored and predictors of missingness examined, especially if these vary by intervention. If necessary, multiple imputation will be used to impute missing data assuming the missingness mechanism is missing at random. A detailed statistical analysis plan will be agreed to before the end of data entry and before the treatment code is broken.

### Plans to give access to the full protocol, participant-level data and statistical code

This document is the full protocol. Anyone interested in other data or documentation should contact the corresponding author.

### Oversight and monitoring

#### Composition of the coordinating centre and Trial Steering Committee

The Trial Management Group consisting of the trial manager, admin staff, Chief Investigator and statistician will meet on a biweekly basis to discuss progress and monitor recruitment, data returns and so on.

The TSC will act as the oversight body for the STARTUP trial on behalf of the sponsor and funders. The group will, through regular reports, be responsible for monitoring recruitment and retention rates and patient safety. They will also advise on future continuation of the trial as well as modifying target recruitment or pre analysis follow-up, based on any change to the assumptions underlying the original trial sample size calculation (but not on any emerging differences).

The group will also oversee the timely completion of the final report and appropriate dissemination. A chair with experience of rehabilitation research has been appointed, and the group also has a statistician, Patient and Public Involvement and a clinically experienced person.

### Composition of the data monitoring committee, its role and reporting structure

It was not felt necessary to have a data monitoring committee in this study for a number of reasons: involves non-critical indication; low risk of harm to patients; and treatment is already available.

### Adverse event (AE) reporting and harms

The STARTUP trial involves treatments that are well established in clinical practice; therefore, AEs (although these are unlikely) will be those observed in everyday practice associated with the condition. Expected AEs arising from the treatments are noted below and thus will not be collected as AEs but noted in the weekly follow-up data collection.

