**Methods and analysis:**

An RCT of 6 weeks with twice weekly TTNS or sham TTNS. Participants will be recruited in 12 National Health Service neurology/movement disorder services, using a web-based randomisation system, and will be shown how to apply TTNS or sham TTNS. Participants will receive a weekly telephone call from the researchers during the intervention period. The trial has two coprimary outcome measures: International Consultation on Incontinence Questionnaire-Urinary Incontinence Short Form and the International Prostate Symptom Score. Secondary outcomes include a 3-day bladder diary, quality of life, acceptability and fidelity and health economic evaluation. Outcomes will be measured at 0, 6 and 12 weeks.

A sample size of 208 randomised in equal numbers to the two arms will provide 90% power to detect a clinically important difference of 2.52 points on the Internatioanl Consultation on Incontinence Questionnaire - Short Form (ICIQ-SF) and of 3 points in the International Prostate Symptom Score total score at 12 weeks at 5% significance level, based on an SD of 4.7 in each arm and 20% attrition at 6 weeks. Analysis will be by intention to treat and pre defined in a statistical analysis plan

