**Ethics and dissemination:**

East of Scotland Research Ethics Service (EoSRES), 18/ES00042, obtained on 10 May 2018. The trial will allow us to determine effectiveness, safety, cost and acceptability of TTNS for bladder dysfunction in PWP. Results will be published in open access journals; lay reports will be posted to all participants and presented at conferences.

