## The intervention

There is a risk of participant unblinding if the intervention or sham intervention is discussed in detail within this protocol; this will be published before trial recruitment is complete. The authors recognise the importance of the allocated intervention being accepted by the participant as the active intervention and have developed the sham intervention to be as realistic as possible yet delivering no intervention.

The treatment protocol developed by Amarenco *et al*
31 will be adopted for this trial.

All participants will use the stimulator for two 30 min sessions a week for 6 weeks. It is preferable to have 2–4 days between stimulation sessions.

A training protocol, including a manual for clinicians and instruction leaflets for participants, has been developed. Participants will be instructed to use the TTNS device twice weekly for 6 weeks with weekly telephone support by research staff.

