### Participant timeline/pathway

The steps within the trial that the participants will take are summarised in box 1.

Box 1The participant pathwayParticipant’s identified at clinic by local PIs, Parkinson’s nurses or research nurses.

Participant information leaflet with expression of interest form attached given/sent to patient along with preaddressed envelope.

Posters also to be put up in relevant clinics to inform patients.Potential participants opt in either by phoning the trial office or by returning the expression of interest form to them.

Staff at the trial office contact participant discuss further the implications of the study and complete screening log. If willing and eligible to be a participant, then the patient is allocated a participant study number and is given an appointment to attend the clinic or for the research nurse to visit them at home (confirmed by trial office with clinic)

At the clinic/home, the participant will be consented, the clinical assessment form will be completed, randomisation will be completed (using the web-based system) and then the participant will be shown how to use the stimulation/placebo stimulation and provided with written instructions.

The participant is given a pack to take home with them containing the 3-day bladder frequency diary (with simple instructions) and the questionnaire booklet. The participant is asked to complete the bladder frequency diary during the next 3 days (starting with the first morning void) before starting to use the stimulation. The pack also contains the bladder diary and a questionnaire booklet to be completed at 6 weeks. Prepaid addressed envelopes will be available.

During the 3 days at home, the research office telephones the participant to support completion of their bladder diary. The participant either completes the questionnaires themselves or over the telephone. These diaries are then posted to the research office. Date when the participant will start using the intervention agreed and the times of the weekly follow-up telephone calls agreed.

Trial office staff will telephone the participant weekly to see how things are going, ask about change in medications, adverse events and so on and will be available for any queries. Trial office will remind/help participant to complete the diary and questionnaires at the end of 6 weeks and will get the participant to unlock the compliance monitor before sending the unit back in the prepaid Jiffy bag.

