#### Urinary tract infection

All AEs and serious AEs will be assessed for seriousness, causality, severity and expectedness and will be reported to the relevant regulatory bodies.

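### Urinary tract infection, the only expected event listed, is kept out of adverse-event collection, and no systematic way to record it in weeks 7 to 12 is stated

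*Protocol article*

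**What the plan says.** All references are to the protocol article.

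- **Adverse event (AE) reporting and harms.** Expected events arising from the treatments "will not be collected as AEs but noted in the weekly follow-up data collection". The one item listed after this is "Urinary tract infection".
- **Text directly under that item.** "All AEs and serious AEs will be assessed for seriousness, causality, severity and expectedness", with reporting to the relevant bodies.
- **Abstract, Methods and analysis.** "Participants will receive a weekly telephone call from the researchers during the intervention period". The same paragraph gives the follow-up schedule: "Outcomes will be measured at 0, 6 and 12 weeks".
- **The intervention.** "Participants will be instructed to use the TTNS device twice weekly for 6 weeks with weekly telephone support by research staff".
- **Participant timeline/pathway (Box 1).** "Trial office staff will telephone the participant weekly to see how things are going, ask about change in medications, adverse events and so on". The same step ends with the 6-week diary and questionnaires and the return of the stimulator. The 12-week contact is described as posting the questionnaires and telephoning to help complete them.
- **Table 2.** There is no row for AEs or UTI. Change in medication is marked weekly and again at week 12. The resource questionnaire is marked at both follow-up points.
- **Abstract, Ethics and dissemination.** "The trial will allow us to determine effectiveness, safety, cost and acceptability of TTNS".

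**The concern.** Two things look wrong.

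First, the harms section sets a rule and then a second rule that does not fit it. If UTI is not collected as an AE, it does not enter the process that assesses AEs. Yet that process is meant to judge expectedness, which makes sense only if expected events can reach it. Staff at 12 sites and the trial office could read this in different ways, most importantly for a UTI that is serious.

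Second, the only place named for recording UTI is the weekly follow-up, and the text ties that contact to the 6 weeks of device use. The hypothesis and the main comparison of the coprimary outcomes are set at 12 weeks.

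At stake is the safety claim. For the one expected event the protocol names, a comparison by arm would be complete at best to week 6, and the non-serious cases would carry no severity or relatedness judgement. An analysis plan written later cannot recover events that were not recorded.

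**Working it through.** No sample-size or power figure bears on this point. The check sets the statements side by side, with one subtraction.

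**Step 1: which events does the exemption cover?** The harms section exempts expected events arising from the treatments. UTI is the only one listed. It appears as a heading, which may be a layout effect, but no other event is named.

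**Step 2: what happens to an exempted event?**

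| Event | Exemption sentence | Assessment sentence | Result as written |
|---|---|---|---|
| Non-serious UTI | Not collected as an AE; noted weekly | Applies to AEs and serious AEs | Not assessed for causality or severity |
| Serious UTI | No mention of seriousness | Names serious AEs explicitly | Unclear |
| Any other AE | Not exempt | Assessed | Assessed |

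The second row is ambiguous. It does not show that serious cases are lost.

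**Step 3: when does the weekly follow-up run?** No single sentence states its end. Three places agree:
- the abstract puts the weekly call in the intervention period;
- the intervention section couples weekly telephone support with 6 weeks of device use;
- Box 1 takes the weekly call up to the 6-week questionnaires and return of the unit, and describes the 12-week contact separately.

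Table 2 is consistent with this. If weekly contact ran to week 12, medication change would not need its own mark there.

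**Step 4: how much follow-up is left?**
- Length of follow-up: 12 weeks (abstract).
- Weekly contact: 6 weeks (Step 3).
- Without stated systematic UTI recording: 12 − 6 = 6 weeks; 6 / 12 = 50%.

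Device use starts after a 3-day baseline diary, so the boundary may move by some days. That does not change the picture.

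**Step 5: what could show a UTI after week 6?** Medication change is recorded at week 12. The 12-week resource questionnaire covers healthcare contacts, medicines and purchases. Either could show a treated UTI, but neither is stated to ask about infection, so a case would have to be inferred. The 12-week call exists, but no AE or UTI question is described for it.

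**The case against.** The strongest case on the other side has five parts.

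- **Serious UTI.** A reader might infer that even a serious UTI escapes assessment. The text does not support that. The exemption concerns collection as AEs, while the next sentence names serious AEs as assessed, so a serious UTI may well be covered. What stands is that the text does not say so.
- **Weeks 7 to 12 are not empty.** A reader might infer that the trial cannot report UTI at all in this period, or that UTI status would be unknown in the 12-week analysis. The medication and resource-use data could reveal treated cases, so both readings go too far. What stands is that there is no stated systematic means of recording UTI.
- **Table 2 proves little by omission.** It also leaves out the weekly AE question that Box 1 describes. That is correct, and the point does not rest on the missing row.
- **Oversight.** A reader might treat the absence of a data monitoring committee as making matters worse. The Trial Steering Committee is charged with monitoring patient safety, so that argument is not relied on.
- **Design choice and condensed article.** Recording treatment-related events only while the device is in use can be defended, and an article often leaves AE windows to fuller documents. But the exemption is a rule the article states, not a detail it leaves out, and the article describes itself as the full protocol. A short recording window also sits poorly with an unrestricted claim to determine safety in a trial that follows participants to week 12.

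**Conclusion.** The point holds in limited form. As written:

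1. non-serious UTIs are not assessed for causality or severity;
2. it is unclear whether a serious UTI is reported as a serious AE;
3. there is no stated systematic recording of UTI for 6 of the 12 weeks, beyond indirect traces.

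UTIs up to week 6 are noted and can be tabulated by arm.

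The third item assumes that weekly contact ends with the intervention period, which is read from three sections together. If the calls in fact continue to week 12, that item falls away and the first two remain.

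No number of missed events is given. It would need a UTI rate, which the documents do not supply, and an assumption about how many cases the week-12 data would fail to show. Nothing here shows bias in the coprimary comparison. UTIs occurring equally in two arms with blinded participants would mainly add noise, and the documents give no reason to expect a difference between arms.

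This should be corrected because the text contradicts itself on a safety matter and the remedy is small. It does not threaten the primary analysis.

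**What to change.** - **Reconcile the two statements in the harms section.** Make explicit, for both arms, how UTI is recorded, whether and how it is assessed for seriousness, causality and severity, how a serious UTI is reported, and over what period.
- **Ask the existing weekly AE/UTI question once more at the planned 12-week telephone contact,** worded to cover the time since the last weekly call.
- **Tabulate UTI by arm to week 12,** separating events noted in the weekly calls from those reported at week 12, since the latter rest on a longer recall period.

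The cost is one added question, a form change and slightly more AE paperwork. No new visit is needed, and sample size and blinding are unaffected. For participants already past week 12 the question cannot be asked on time, so the report should state the recording window that applied to them.

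An analysis that drops outcome scores taken during a UTI is not recommended as part of this fix. It selects on an event after randomisation and would be supportive at most.

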#### Urinary tract infection

All AEs and serious AEs will be assessed for seriousness, causality, severity and expectedness and will be reported to the relevant regulatory bodies.

### Frequency and plans for auditing trial conduct

The TSC will meet every 6 months.

### Ethics and dissemination

The study is sponsored by Glasgow Caledonian University, and the START-UP trial office is based in the Nursing, Midwifery and Allied Health Professions Research Unit.

Participants have the right to withdraw from the study at any time and for any reason, and all participants are made aware that withdrawal will not affect their routine care.

## Dissemination

Our dissemination plan is designed to achieve maximum study exposure and impact among a range of beneficiaries (PwP and carers, healthcare professionals, national/local decision makers, professional bodies, patient/carer organisations and the academic research community). Dissemination strategies will include presentations at a range of Parkinson’s disease/dementia/neurology and continence (bladder and bowel) related professional and research conferences. A final report will be submitted to Dunhill Medical Trust and Parkinson’s UK. A summary of the findings will be provided to all study participants (if requested). The main results paper will target a high-impact journal (eg, *BMJ* and *Movement Disorders*), while other papers (eg, methodology and health economics) will target relevant open access journals. Authorship and time scales will be agreed by the project management team. Findings will be provided to NICE and Cochrane Reviews for guideline updates for bladder and bowel dysfunction, diagnosis and management of Parkinson’s disease in primary and secondary care, local guidelines and care pathways and relevant Cochrane Reviews and updates. We will use Twitter to share study news and exploit other relevant social media to raise awareness of study progress and the findings, as well as press releases to news media.

### Plans for communicating important protocol amendments to relevant parties (eg, trial participants and ethical committees)

Funders, sponsors and NHS Research & Development Offices will be notified routinely and appropriate approvals gained and communicated as required by them and by the trial sponsor.

## Discussion

This study is a pragmatic patient-oriented trial aiming to capture a true representation of the actual patient population of interest. We know from previous work and from reviews that there is a lack of evidence-based interventions for bladder dysfunction in PwP. The cost to the NHS and to the patient is considerable, and the effect on QOL both for patients and carers is significant and disabling. The lack of robust evidence on effective management leads to inconsistent advice and confused management pathways. Parkinson’s disease is a long-term condition, and supported self-management is important. TTNS as an adjunct to treatment offers a safe, non-invasive and non-drug intervention that can be undertaken by the patient or a carer at home. As such it is likely to be an attractive option for many. Should the trial demonstrate that TTNS is effective, we feel that an integration into standard local pathways should be possible, as the training required for clinicians and patients (or carers) is minimal.

### Trial status

Subject recruitment is underway. Currently 12 sites are recruiting, and we are ahead of target. The first participant was randomised in October 2018, and recruitment is due to end in June 2020. The TSC has met twice. The trial registration number is https://doi.org/10.1186/ISRCTN12437878.
